#### Calculation of sample size

According to the results of previous studies, for patients undergoing lobectomy with tumour sizes of 2–3 cm, CTR≤0.5 and the 5 year DFS was 97.0% after surgery.^13^ In this trial, we assumed that the expected 5 year DFS for these patients undergoing segmentectomy is 95%. A sample size of 292 achieves 90.193% power to detect a non-inferiority proportion of 90% (5% as the non-inferior boundary) using a one-sided exact test with a target significance level of 0.0250. Considering a possible dropout rate of 5%, a total of 307 cases need to be included in this trial.

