### Endpoints

The primary endpoint is 5 year disease-free survival (5 year DFS). DFS events are defined as tumour recurrence due to lung cancer or death from any cause. Alive patients without recurrence at the last follow-up are defined as censored.

The secondary endpoints are lung function, 5 year overall survival, the site of tumour recurrence and metastasis, segmentectomy completion rate, radical segmentectomy (R0 resection) completion rate and surgery-related complications.

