### Statistical analysis

#### Analysis sets

Full analysis set (FAS): determined according to the intention-to-treat principle, including all enrolled cases who have undergone segmentectomy.

Per-protocol set (PPS): subset of the FAS population, including all cases that meet the protocol and have completed case report form.

In this trial, FAS analysis is used for baseline data and validity analysis. The main efficacy indicators are will be analysed in the FAS and PPS data sets. However, the analyses of the FAS data set are considered primary. When analyses of the FAS and PPS reach consistent conclusions, confidence in the conclusions can be increased. For the FAS data set, the missing data after the fall are estimated using the last observation carried forward method.

The laboratory examination data and adverse events will be analysed using SPSS and Stata software.

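### The 90.193% power is right for 292 patients of known 5-year status, but the design as described does not deliver it: about 88% if dropouts are excluded, or a type I error of about 4% if they are carried forward as disease-free

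*Protocol article*

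**What the plan says.** Under *Calculation of sample size*, the protocol article tests a "non-inferiority proportion of 90% (5% as the non-inferior boundary"), with an expected 5-year DFS of 95%, "using a one-sided exact test with a target significance level of 0.0250". It reports that "A sample size of 292 achieves 90.193% power to detect a non-inferiority proportion of 90" per cent, and then: "Considering a possible dropout rate of 5%, a total of 307 cases need to be included in this trial".

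Under *Endpoints*: "The primary endpoint is 5 year disease-free survival (5 year DFS"). Events are recurrence or death from any cause, and "Alive patients without recurrence at the last follow-up are defined as censored".

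Under *Analysis sets*, the full analysis set (FAS: enrolled patients who underwent segmentectomy) is primary, and "For the FAS data set, the missing data after the fall are estimated using the last observation carried forward method".

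The Abstract gives 5 years for enrolling 307 patients. *Study design* gives a February 2023 start, with estimated primary completion in December 2028 and study completion in December 2029. Apart from the exact test in the sample-size paragraph, the article names no test or estimator for the primary endpoint.

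**The concern.** Four statements bear on the same primary result: an exact binomial test for sizing, a DFS definition with censoring, a carry-forward rule for missing data, and a follow-up calendar. They do not fit together. An exact binomial test treats each patient as a known success or failure at 5 years. A patient censored at 3 years is neither, so something must be done with that patient, and the stated power and significance level hold together under none of the obvious choices.

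This is a single-arm confirmatory trial judged against one fixed threshold, 90%. With only about 20 events permitted, the handling of a few incomplete patients can move the result across that threshold. At stake are a power figure that is somewhat optimistic and, under one reading of the text, a significance level well above the one stated.

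**Working it through.** **Inputs.** Null p0 = 0.90, alternative p1 = 0.95, one-sided alpha = 0.025, n = 292, dropout 5%, 307 enrolled (all from *Calculation of sample size*).

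**Step 1: reproduce the stated figure.** For each n, find the smallest r with P(X ≥ r | n, 0.90) ≤ 0.025. Power is then P(X ≥ r | n, 0.95). At n = 292, r = 273 (at most 19 events), the attained alpha is 0.0242 and power is 0.90193. The plan's figure is exact.

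**Step 2: neighbouring sample sizes.**

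| Evaluable n | Events allowed | Attained alpha | Power |
|---|---|---|---|
| 280 | 18 | 0.0241 | 0.888 |
| 291 | 18 | 0.0148 | 0.855 |
| 292 | 19 | 0.0242 | 0.902 |
| 293 | 19 | 0.0232 | 0.899 |
| 303 | 19 | 0.0150 | 0.872 |
| 304 | 20 | 0.0243 | 0.914 |
| 307 | 20 | 0.0214 | 0.907 |

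From 280 to 303, only 292 reaches 90%. From 304 to 307 power is above 90% again.

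**Step 3: dropouts excluded.** Expected evaluable: 307 × 0.95 = 291.65. Let K ~ Binomial(307, 0.95) and re-derive r at each K.
- Mean power = 0.8805, and 0.9019 − 0.8805 = 0.021.
- P(K < 292) = 0.469.
- P(K = 292) = 0.1046 and P(K ≥ 304) = 0.0001, so the probability that power is below 90% is 1 − 0.1046 − 0.0001 = 0.895.

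**Step 4: dropouts kept in the FAS and carried forward as disease-free.** Assume 5% drop out at random and none of their events is seen. The apparent disease-free proportion is then 0.95p + 0.05.
- Under the null: 0.95 × 0.90 + 0.05 = 0.905. Under the alternative: 0.95 × 0.95 + 0.05 = 0.9525.
- With n = 307 and r = 287, type I error = P(X ≥ 287 | 307, 0.905) = 0.0405, and power = P(X ≥ 287 | 307, 0.9525) = 0.938.

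If dropouts are spread over the 5 years, some of their events are seen before loss and the inflation is smaller.

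**Step 5: an analysis that respects censoring.** Kaplan-Meier at 5 years, 307 patients, exponential event times, 5% loss over 5 years and everyone else followed to 5 years (20,000 simulated trials), with the one-sided 97.5% lower bound compared with 90%:

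| Interval | Power | Type I error |
|---|---|---|
| Complementary log-log | 0.88 | 0.020 |
| Log | 0.95 | 0.048 |
| Plain | 0.95 | 0.046 |

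The choice of interval matters: of these three, only the complementary log-log bound keeps type I error below 0.025.

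**Step 6: the calendar.** Assume uniform accrual over 5 years from mid-February 2023. December 2028 is then about 5.87 years after the start and December 2029 about 6.87.
- Share with a full 5 years of follow-up: (5.87 − 5)/5 = 17%, and (6.87 − 5)/5 = 37%.
- With a constant low hazard, and ignoring other losses, the variance of the cumulative hazard at 5 years grows by about [0.87 + 5 ln(5/0.87)]/5 = 1.92 at the earlier date, and by [1.87 + 5 ln(5/1.87)]/5 = 1.36 at the later one.
- In precision, 307 patients then act like roughly 307/1.92 = 160 or 307/1.36 = 226 fully followed patients, so the 88% of step 5 does not apply.

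**The case against.** The strongest reply is that nothing is miscalculated. The plan claims 90.193% for 292, and that is right to every digit. Choosing the smallest n that reaches the target is routine, and every exact-test design has a sawtooth. This stands: a reader might infer an arithmetic error, and there is none.

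Second, a reader might infer that the power holds only with exactly 292 patients. It does not, because 304 to 307 also exceed 90%. With 5% random dropout, however, the chance of 304 or more evaluable patients is about 0.0001.

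Third, the 88% of step 3 presumes that dropouts are excluded, while the FAS is primary and has a carry-forward rule. This is fair, and it is why step 4 is needed. With all 307 statuses truly known, power would be 90.7% at an attained alpha of 0.0214. Keeping 307 by counting dropouts as disease-free raises power only by loosening the error rate.

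Fourth, sizing on a proportion and analysing by Kaplan-Meier is common, and an analysis plan not shown may do so. One therefore cannot infer that censored patients will be discarded or that the exact test is the final analysis; the article says neither. But if the analysis is Kaplan-Meier with a log-log bound, 90.193% is the power of a different test, and the carry-forward sentence still conflicts with the censoring rule.

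Fifth, 307 rather than 308 is trivial. 292/0.95 = 307.4, while 292 × 1.05 = 306.6 gives 307 by a common convention. Enrolling 308 lifts mean power only to 88.3%. The rounding is not part of this point.

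**Conclusion.** The point holds in limited form. The stated power is correct for the test and number it names, but the rest of the design does not lead to that test on that number. Excluding dropouts gives a mean of about 88%. A log-log Kaplan-Meier analysis with 5% loss also gives about 88%. Carrying dropouts forward as disease-free gives about 94%, with type I error of about 4% instead of 2.5%.

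The average power loss, about 2 points, is small; the 85.5% at 291 is the bottom of the sawtooth and should not be read as the expected power. The weightier part is the mismatch between a test that needs complete binary status, a censored endpoint and a carry-forward rule.

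These figures assume a true DFS of 95% (90% for type I error), dropout of 5% unrelated to prognosis, and complete 5-year follow-up otherwise. The 4% further assumes that the carry-forward rule reaches DFS, which the article does not say outright, and that no dropout's event is observed. If the stated dates mean analysis in December 2028 with accrual spread over 5 years, most patients are censored before 5 years and power is much lower than 88%.

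**What to change.** - Name the primary test: Kaplan-Meier 5-year DFS in the FAS, with success if the one-sided 97.5% complementary log-log lower bound exceeds 90%.
- State that last observation carried forward is not applied to DFS; patients without an event are censored as *Endpoints* already defines.
- Replace the 90.193% claim with power of about 88% for 307 enrolled, conditional on 5% loss and every other patient being followed for 5 years.
- Reconcile that condition with the 5-year accrual period and the December 2028 primary completion date. Either tie the primary analysis to completed 5-year follow-up, or restate the power for the follow-up that will exist at the planned date.

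The cost is wording in the sample-size and analysis-set sections, and a stated power about 2 points less favourable. No change in enrolment is needed if about 88% is acceptable. If a 90% mean is wanted from the exact test with dropouts excluded, about 325 would have to be enrolled. Tying the analysis to complete follow-up may move the primary completion date.

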### Data access

The Data Management Coordinating Centre will oversee the intrastudy data- sharing process, with input from the Data Management Subcommittee. All Principal Investigators will be given access to the cleaned data sets. Project data sets will be housed on the Project Accept website and/or the file transfer protocol site created for the study, and all data sets will be password-protected. Project Principal Investigators will have direct access to their own site’s data sets and will have access to other sites’ data by request. To ensure confidentiality, data dispersed to project team members will be blinded to any identifying participant information.

### Patient and public involvement

None.

## Ethics and dissemination

The protocol and informed consent form have been reviewed and approved by the Ethics Committee of Fudan University Shanghai Cancer Centre (reference 2212267-18) and by the institutional review boards of each participating centre. Only patients who can fully understand the risks, benefits and potential adverse events of this trial will be enrolled after voluntarily signing an informed consent form (online supplemental Material 1). Informed consent should be in line with the Declaration of Helsinki.

10.1136/bmjopen-2024-087088.supp1Supplementary data

The personal data collected and processed by the patients enrolled in this study will be limited to those necessary to complete the purposes of this study.

The results of the trial will be updated on ClinicalTrials.gov, published in peer-reviewed journals and presented at international academic conferences.
